#### Qualitative data analysis

Interviews and focus-groups will be audio-recorded using encrypted digital voice recorders, transcribed verbatim and anonymised. *Nvivo* v.10 software will be used to code and manage qualitative data. First level analysis will be deductive, guided by the research questions, and peer researchers will be consulted for input and feedback during the analytical process.^94^ A constant comparison method will be used to develop the thematic analysis and will reflect diverging and converging narratives, for example, across groups of intervention recipients at different time points in the treatment pathway, or between groups of intervention providers.^94^ The findings will be contextualised in the relevant theoretical perspectives which may include the diffusion of preventive innovations (staff) or social norms and values that might underpin health behaviour (recipients).^95 96^ We will assess TasP both from the providers’ perspective and from patients’ perspective including those who refuse treatment.

We will use the findings iteratively to update the HCV TasP logic model shown in figure 5. Our qualitative data will be used to generate a manual of an optimal intervention for other sites in UK. In previous examples, such as (https://www.youtube.com/channel/UCBV8smLmkOQVT9D0OR-md1g/videos) we have used the Behaviour Change Wheel^96^ as the framework to retrospectively analyse the success and failure of implementation within Tayside and then prospectively to formulate the optimal implementation intervention.

**Figure 5 F5:**
[figure not shown]
Preliminary logic model HCV treatment as prevention (EPIToPe). HCPs, healthcare providers; HCV, hepatitis C virus; HCWs, healthcare workers; Hep-C, hepatitis C; NHS, National Health Service; NSP, needle and syringe programmes; TasP, Treatment as Prevention; PWID, people who inject drugs.

### Mixed method study on drug use outcomes: OST retention, drug overdose, recovery and social transformation

Health Protection Scotland (HPS) link data on diagnostic HCV tests in the four largest Scottish NHS boards (including Tayside)^8^ and all persons undergoing HCV treatment in the Scottish HCV Clinical database^97^ which are also linked with other databases (including deaths, hospitalisations and drug treatment)^8 42 98–100^ and from 2018 Scotland's Prescribing Information System which holds data on OST and NHS prison health database (Prison Vision).^101–105^ PWID attending drug services who were HCV diagnosed, compared with those who were not, are at increased risk of drug-related and other cause-specific morbidity/mortality.^106 107^ Thus, we will create a virtual cohort of chronic HCV infected PWID (estimated to involve at least 600 individuals from Tayside and 3000 from elsewhere) and through linkage identify those who have been treated and attained SVR with those who have not. We will assess and compare the following outcomes: retention in drug treatment (determined through linkage to drug treatment and prescribing databases), drug-related and alcohol-related morbidity/mortality (through linkage to all hospital admission and mortality databases) and other markers of relapse (through linkage to prisons database).

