## Abstract

**Introduction:**

Hepatitis C virus (HCV) is the second largest contributor to liver disease in the UK, with injecting drug use as the main risk factor among the estimated 200 000 people currently infected. Despite effective prevention interventions, chronic HCV prevalence remains around 40% among people who inject drugs (PWID). New direct-acting antiviral (DAA) HCV therapies combine high cure rates (>90%) and short treatment duration (8 to 12 weeks). Theoretical mathematical modelling evidence suggests HCV treatment scale-up can prevent transmission and substantially reduce HCV prevalence/incidence among PWID. Our primary aim is to generate empirical evidence on the effectiveness of HCV ‘Treatment as Prevention’ (TasP) in PWID.

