**Methods and analysis:**

We plan to establish a natural experiment with Tayside, Scotland, as a single intervention site where HCV care pathways are being expanded (including specialist drug treatment clinics, needle and syringe programmes (NSPs), pharmacies and prison) and HCV treatment for PWID is being rapidly scaled-up. Other sites in Scotland and England will act as potential controls. Over 2 years from 2017/2018, at least 500 PWID will be treated in Tayside, which simulation studies project will reduce chronic HCV prevalence among PWID by 62% (from 26% to 10%) and HCV incidence will fall by approximately 2/3 (from 4.2 per 100 person-years (p100py) to 1.4 p100py). Treatment response and re-infection rates will be monitored. We will conduct focus groups and interviews with service providers and patients that accept and decline treatment to identify barriers and facilitators in implementing TasP. We will conduct longitudinal interviews with up to 40 PWID to assess whether successful HCV treatment alters their perspectives on and engagement with drug treatment and recovery. Trained peer researchers will be involved in data collection and dissemination. The primary outcome – chronic HCV prevalence in PWID – is measured using information from the Needle Exchange Surveillance Initiative survey in Scotland and the Unlinked Anonymous Monitoring Programme in England, conducted at least four times before and three times during and after the intervention. We will adapt Bayesian synthetic control methods (specifically the Causal Impact Method) to generate the cumulative impact of the intervention on chronic HCV prevalence and incidence. We will use a dynamic HCV transmission and economic model to evaluate the cost-effectiveness of the HCV TasP intervention, and to estimate the contribution of the scale-up in HCV treatment to observe changes in HCV prevalence. Through the qualitative data we will systematically explore key mechanisms of TasP real world implementation from provider and patient perspectives to develop a manual for scaling up HCV treatment in other settings. We will compare qualitative accounts of drug treatment and recovery with a ‘virtual cohort’ of PWID linking information on HCV treatment with Scottish Drug treatment databases to test whether DAA treatment improves drug treatment outcomes.

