#### HCV treatment

Apart from expansion of community HCV care pathways, no new clinical procedures will be investigated and all PWID with chronic HCV will be offered oral DAA HCV treatment compliant with the Scottish clinical guidelines (https://www.hps.scot.nhs.uk/resourcedocument.aspx?id=6621).

As per local standard of care, participants will be offered appropriate harm reduction advice.

Standard care for patients is to test for SVR at 12 weeks after end of treatment with patients being recommended for annual follow-up if at risk of re-infection. Specialist nurses concentrate on building a good relationship with the participant to ensure that they do return for follow-up appointments. Health Protection Scotland collates national public health surveillance data on the number, characteristics and response of patients initiated onto HCV therapy, through Clinical Databases installed in 17 specialist HCV treatment centres, across Scotland.^41 86^ A similar system also is available in England.

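### The virtual cohort is grouped by attained SVR although its stated aim is the effect of DAA treatment, so the contrast selects on survival and engagement in care

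*Protocol article*

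**What the plan says.** The section on the mixed method study of drug use outcomes plans a linked cohort of PWID with chronic HCV, "estimated to involve at least 600 individuals from Tayside and 3000 from elsewhere". It will "through linkage identify those who have been treated and attained SVR with those who have not". The outcomes to be compared are "retention in drug treatment (determined through linkage to drug treatment and prescribing databases"), drug- and alcohol-related morbidity and mortality, and "other markers of relapse (through linkage to prisons database").

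The Abstract (Methods and analysis) describes the purpose of the same cohort as "linking information on HCV treatment with Scottish Drug treatment databases to test whether DAA treatment improves drug treatment outcomes".

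On timing, the Abstract (Introduction) gives a course of 8 to 12 weeks, and the HCV treatment section says "Standard care for patients is to test for SVR at 12 weeks after end of treatment". That section also describes nurses working to get patients back for follow-up, so attendance is not taken for granted.

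The article does not state a time zero for either group, or whether exposure is fixed or time-varying. Nor does it say where treated people with a failed or missing SVR test are placed.

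**The concern.** The groups are defined by a result obtained after treatment, while the Abstract asks about treatment itself. To be counted as having attained SVR, a person must start treatment, live through the course and a further 12 weeks, and normally return for the test. Someone who dies or leaves care in that interval cannot enter the SVR group. Those events are, or lie close to, the retention and mortality outcomes being compared.

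The reported cure rate is above 90%, so true virological failures should be few. Treated people without a recorded SVR may therefore include a sizeable share who died, dropped out or did not return; the article does not give that share. Recorded SVR is then partly a marker of engagement.

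At stake is whether better retention or survival in the SVR group could be read as a benefit of DAA treatment.

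**Working it through.** The article gives no effect size, event rate or power for the virtual cohort, so there is no stated figure to reproduce.

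**1. Earliest time at which SVR can be recorded.** Inputs: course of 8 to 12 weeks (Abstract, Introduction); test 12 weeks after the end of treatment (HCV treatment section).
- Shortest: 8 + 12 = 20 weeks (20/52 = 0.38 years).
- Longest: 12 + 12 = 24 weeks (24/52 = 0.46 years).

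**2. Simple illustration under no effect.** Assume a constant, low event rate in everyone, a clock starting at treatment, an event that would prevent a recorded SVR, and the pre-SVR weeks counted as SVR follow-up. The SVR group then has events only in the remaining weeks, so rate ratio ≈ (follow-up − wait) / follow-up.
- 2 years: (104 − 20)/104 = 0.81; (104 − 24)/104 = 0.77.
- 1 year: (52 − 20)/52 = 0.62; (52 − 24)/52 = 0.54.

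**3. Null simulation (true rate ratio 1; 200,000 people per scenario).** Assumptions not in the article: 60% due for treatment, 95% cure, 2 years of follow-up, annual event risk of 5%, 20% or 40%, any event before the test prevents a recorded SVR, and everyone without SVR is in the comparator.

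| Analysis | Treatment starts | Null rate ratio |
|---|---|---|
| SVR vs all others, fixed groups, clock from cohort entry | almost at once | 0.53 to 0.61 |
| Same | spread over 0.5 year | 0.41 to 0.45 |
| Same | spread over 1 year | about 0.33 |
| Ever vs never treated, fixed groups, clock from cohort entry | spread over 1 year | 0.50 to 0.54 |
| Exposed only after SVR (time-varying) | all spreads | 0.98 to 1.01 |
| Exposed from treatment start, whatever the SVR result (time-varying) | all spreads | 0.99 to 1.01 |

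At 20% annual risk with starts spread over 1 year, the fixed SVR grouping shows 2-year risks of 21.7% against 48.6% with no true effect.

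**4. Adding unmeasured frailty** (assumed log-SD 1, starts spread over 1 year). Time-varying SVR gives 0.79 to 0.95; time-varying treatment start gives 0.84 to 0.96.

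Steps 2 and 3 show that the time-related part depends on how exposure time is coded and disappears when it is coded correctly. The ever-versus-never row shows that changing the exposure to treatment is not enough unless follow-up is also aligned. Step 4 shows that selection into treatment persists under either exposure, somewhat more with SVR.

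**The case against.** The strongest reply is that the article has not committed to a biased analysis. Time origin and exposure coding are commonly left to an analysis plan, and entry at SVR or time-varying exposure would remove the immortal time. That stands. A reader might infer that immortal time is built in and that the study is bound to show benefit; the text supports neither inference. Nor does it say that everyone without SVR is the comparator. The sentence is ungrammatical, and the comparator could be untreated people, treated people without SVR, or both.

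SVR also has a legitimate role. The Introduction and background section frames the hypothesis as one about successful HCV treatment and says the virtual cohort will be compared with the qualitative findings on it. Grouping by SVR fits that question. It does not fit the Abstract's question about DAA treatment.

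The direction of bias is not uniform either. A hospital admission or a prison spell need not prevent SVR from being recorded. Prison is both a treatment site and the source of a relapse marker, so bias on that marker could run either way.

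Finally, a reader might set the cohort sizes side by side and infer that exposure is almost the same thing as region. The documents do not support this: the 3000 is the whole cohort outside Tayside, and the linked clinical database covers all persons treated in Scotland, so treated people elsewhere are included.

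What remains is that fixing time zero alone would neither remove selection on engagement nor make an SVR-defined group answer a question about DAA treatment.

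**Conclusion.** The concern holds in a limited form. The stated grouping does not match the Abstract's aim, and it conditions on survival and engagement for at least 20 to 24 weeks after treatment start. Bias towards SVR on retention and mortality is likely under either of two conditions: treated people without a recorded SVR fall into the comparator, or pre-SVR time is credited to the SVR group. The article neither states nor excludes these.

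The 0.77 to 0.81 over 2 years is an illustration resting on a constant hazard, events that block SVR, and pre-SVR time counted as exposed. It is not an estimate of the bias this study will have. The simulated values are likewise conditional on the assumptions listed.

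The virtual cohort is a secondary study; the primary outcome, chronic HCV prevalence among PWID in the community, is untouched.

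**What to change.** State which question each contrast answers, who the comparator is, and when follow-up starts.

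- **DAA-treatment question.** Make DAA initiation the exposure, either time-varying or with follow-up of initiators and non-initiators aligned at a common eligibility date and people classified only by what has happened up to that date. Keep all initiators in the treated group whatever their SVR result, including those never tested. Adjust for OST status, prison status and prior admissions before initiation, and for health board.
- **Successful-treatment question.** Keep SVR versus no SVR as a secondary landmark analysis from the SVR test date, among treated people still in follow-up, and report how many treated people were never tested.

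The cost is wording in the analysis plan and a correction to the sentence defining the groups; the linked databases the study plans to use should hold the dates needed. The estimate will probably be smaller. The landmark analysis will have few people without SVR if cure exceeds 90%. Residual confounding by selection into treatment remains and should be acknowledged.

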Prevention of hepatitis C disease and HCV transmission is now possible because highly effective, tolerable, short-course interferon-free direct-acting antiviral therapies (DAAs) are available for all HCV genotypes with cure rates – defined as sustained virological response (SVR) - exceeding 90%.^27–29^ We, and others, hypothesise that HCV treatment scale-up for PWID, and resulting HCV Treatment as Prevention (TasP) could enhance other primary interventions and reduce HCV incidence and chronic prevalence to negligible levels (ie, towards elimination as a major public health concern).^30–35^ TasP refers to the concept whereby future transmission is reduced by treating affected individuals^36 37^: in HIV TasP antiretroviral treatment reduces transmission because individuals have undetectable infection^38^ in HCV TasP people are cured so reducing opportunities for future transmission. WHO targets for HCV elimination, adopted by UK and other countries, aim to reduce HCV incidence by 80% and associated mortality by 65% by 2030.^39–44^

Clinical guidelines in Europe and USA changed from recommending prioritising HCV treatment to people with moderate-to-severe liver disease towards removing any restrictions and recommending that people at risk of transmission irrespective of fibrosis stage are offered treatment.^45–49^ Cost-effectiveness models that incorporate the population prevention benefit suggest early treatment should be prioritised to PWID over other patient groups (unless chronic HCV prevalence and transmission is very high).^50^ There is direct evidence that SVR following HCV treatment reduces liver disease progression and mortality risk,^51–53^ but in two recent reviews we found no empirical evidence that HCV treatment scale-up has reduced chronic HCV prevalence and incidence in PWID populations.^36 37^ In part this is because in most settings HCV treatment rates in PWID are too low and any changes generally too small to be detected, as we show in two studies of seven sites in UK^7^ and an extension to 11 sites in Europe.^54^ Until very recently in the UK, the annual number of HCV DAA treatments was restricted - as drug costs could be expensive (>£10 000 per patient). There is the opportunity now to test whether scaling up HCV treatment will reduce chronic HCV prevalence and transmission among PWID.^44^

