Finally it has been hypothesised that successful HCV treatment in PWID may positively impact on understandings of self and identity and improve treatment of drug use disorders.^71 72 78–80^ Accounts of ‘transformative’ outcomes extending beyond viral clearance alone include reference to reductions in drug and alcohol use, uptake of safer injecting practices, improved social relationships, enhanced sense of responsibility and self-worth. Hints of such collateral or indirect benefits are also found in quantitative studies reporting low re-infection rates and reductions in risky injecting behaviours among treated PWID.^81 82^ We aim to test this hypothesis in our qualitative follow-up study and compare the findings to quantitative data generated from a virtual cohort.

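### Alcohol-related morbidity and mortality, used as a relapse marker after cure, can as worded include liver disease that cure itself reduces

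*Protocol article*

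**What the plan says.** The Introduction of the protocol article sets out the hypothesis that "successful HCV treatment in PWID may positively impact on understandings of self and identity and improve treatment of drug use disorders". Among the changes it has in mind, beyond clearing the virus, is less use of drugs and alcohol. The authors will test this in the qualitative follow-up study and "compare the findings to quantitative data generated from a virtual cohort". The Abstract gives the cohort's purpose as "to test whether DAA treatment improves drug treatment outcomes".

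The section on the mixed method study of drug use outcomes describes the cohort ("estimated to involve at least 600 individuals from Tayside and 3000 from elsewhere") and its contrast: linkage will "identify those who have been treated and attained SVR with those who have not". Three groups of outcomes are listed:

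- retention in drug treatment;
- "drug-related and alcohol-related morbidity/mortality (through linkage to all hospital admission and mortality databases";
- "other markers of relapse (through linkage to prisons database".

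The section lists no causes or codes for the second group and does not mention the liver. Elsewhere in the Introduction the article states: "There is direct evidence that SVR following HCV treatment reduces liver disease progression and mortality risk".

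**The concern.** The groups are defined by SVR, and the outcome is read as behaviour. The third outcome group is introduced as *other* markers of relapse, so the morbidity and mortality group before it is meant as a relapse marker too. The section heading, which speaks of recovery and social transformation, points the same way.

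In a cohort in which everyone has chronic HCV, the ordinary meaning of alcohol-related illness and death takes in liver disease attributed to alcohol. By the article's own account, cure acts on liver disease directly. An outcome that counts such events can improve through virology alone.

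Adjustment for confounders or a larger cohort would not remove this, because the liver effect is a real effect of cure that arrives by a different route from the one under test. A lower alcohol-related rate could then be taken as support for the recovery hypothesis, and as agreement with the interview accounts, when it only restates an effect the article already treats as known.

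**Working it through.** The article gives no event count, effect size or power for this outcome, so there is no figure of its own to reproduce. The calculation below only illustrates how far the liver route could move the result.

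**Inputs, all assumed**
- s: share of liver events among the alcohol-related events counted in the uncured group.
- RR: rate ratio for those liver events, cured versus uncured. The article says cure lowers this risk but gives no size.
- Behavioural effect: none, so the rate ratio for non-liver events is 1.

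**Apparent rate ratio**

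Apparent ratio = (1 - s) × 1 + s × RR = 1 - s(1 - RR)

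- s = 0.20, RR = 0.7: 1 - 0.20 × 0.30 = 0.94
- s = 0.60, RR = 0.4: 1 - 0.60 × 0.60 = 0.64

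A wider grid:

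| s | RR = 0.3 | RR = 0.5 | RR = 0.7 |
|---|---|---|---|
| 0 | 1.00 | 1.00 | 1.00 |
| 0.1 | 0.93 | 0.95 | 0.97 |
| 0.2 | 0.86 | 0.90 | 0.94 |
| 0.3 | 0.79 | 0.85 | 0.91 |
| 0.5 | 0.65 | 0.75 | 0.85 |

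**Chance of a significant but spurious benefit**

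This uses the Schoenfeld approximation with E total events, half the cohort cured (assumed) and a two-sided 5% level:

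Chance = Φ(|ln(apparent ratio)| × √(E/4) - 1.96)

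For E = 400, √(E/4) = 10. An apparent ratio of 0.91 gives |ln 0.91| × 10 = 0.943, and Φ(0.943 - 1.96) = 0.155. The ranges below run from RR = 0.7 to RR = 0.3. The nominal rate in the benefit direction is 2.5%.

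| s | E = 200 | E = 400 | E = 800 |
|---|---|---|---|
| 0.1 | 4% to 7% | 5% to 11% | 6% to 18% |
| 0.3 | 10% to 39% | 16% to 65% | 27% to 92% |
| 0.5 | 21% to 86% | 37% to 99% | 63% to 100% |

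The approximation treats events as first events with proportional hazards and looks at the liver route alone.

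**After the change**

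With liver causes taken out of the outcome, s = 0. The apparent ratio is then 1.00 whatever RR is, and the liver route contributes nothing.

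**The case against.** The strongest reply is that the article never says liver disease is counted. Naming all admission and death databases identifies the data source and does not mean that every cause attributable to alcohol enters the outcome. The definition may already be limited to intoxication, dependence or poisoning, and code lists are commonly left to a full protocol or analysis plan, which is not shown here. This stands in part. A reader might infer that the outcome does include liver disease and that a liver benefit would be misread as recovery. The text supports neither as fact. It supports only that the outcome can include such events and could then be misread. The point is nevertheless more than an unprinted code list: a list entirely faithful to the stated construct could still carry the bias, because the construct itself does not separate the two routes.

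The second reply concerns time. The Introduction describes liver cancer and premature death from HCV as arising over 20 to 40 years, and the Discussion says that benefit accrues over a prolonged period. The scale-up began in 2017. The follow-up of the virtual cohort is not stated, but a short one makes a large liver share and a strong liver effect less likely. This stands, and it favours the milder end of the range.

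The third reply is that liver events also say something about continued drinking, so dropping them discards relevant information. This also stands and is reflected in the fix.

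A reader might also extend the point to drug-related morbidity, on the idea that viral hepatitis codes are counted there. Nothing in the article supports that.

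**Conclusion.** The point holds in conditional form. As worded, the alcohol-related outcome can include liver disease attributed to alcohol. It is used as a relapse marker in a contrast defined by SVR, and the article itself says SVR reduces liver disease progression and mortality. If liver causes are counted, the outcome cannot tell a liver effect from a change in drinking, and the bias runs towards the hypothesis.

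The size is uncertain. With no behavioural effect, the apparent rate ratio would be 0.94 at an assumed liver share of 20% and liver rate ratio of 0.7. The value of 0.64, at 60% and 0.4, is an extreme over short follow-up. If no liver causes are counted, there is no bias from this source. Shares, rate ratios, event counts and the even split are all assumptions.

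The reach is limited to the alcohol component of one secondary outcome. Retention in OST, overdose, the prison markers and the primary outcome of chronic HCV prevalence are not affected.

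**What to change.** For the recovery hypothesis, state before the linked outcome data are examined that:

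1. the main alcohol outcome is non-hepatic alcohol-related events: intoxication, dependence or withdrawal, and alcohol-related injury or poisoning;
2. liver admissions and deaths are reported separately, as the expected direct effect of cure;
3. the full alcohol-related composite, liver events included, is a sensitivity analysis, since liver events also carry some signal of continued drinking.

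If the full protocol or analysis plan already confines the outcome to non-hepatic causes, a sentence saying so is enough.

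The change needs only a cause list applied to data that will be linked anyway, and no new collection. The price is fewer events and so less precision on this one component. Fixing the split in advance matters, because a split made after the results are known would look selective.
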